### Aims and objectives

Our aim is to evaluate the efficacy and safety of oral functional fatty acids as a potential nonsurgical approach for promoting the expulsion of small gallstones.

Our specific primary objective is to compare the complete expulsion rate of small gallbladder stones at day 3 post-intervention between the two groups, as confirmed by two independent blinded ultrasound technologists. A key secondary objective is to compare the complete expulsion rate at day 6 post-intervention to evaluate the effect of treatment duration.

In addition, we will determine the incidence and severity of treatment-related adverse events (such as gastrointestinal symptoms and abdominal pain) in the treatment group according to the Common Terminology Criteria for Adverse Events (CTCAE) Version 5.0. In addition, we will evaluate the safety of the oral functional fatty acids by measuring changes in key biochemical markers before and after the intervention, including serum alanine transaminase (ALT), aspartate transaminase (AST), and total cholesterol. ALT and AST are sensitive markers of hepatocellular injury, and their measurement is necessary to assess whether oral administration of large volumes of fatty acids imposes excessive metabolic burden on the liver. Total cholesterol levels will be monitored to detect any adverse effects on lipid metabolism, as well as to evaluate potential changes in bile lipid composition that may contribute to gallstone formation or dissolution.

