### Trial design

This is a parallel-group randomized controlled superiority trial with a 1:1 allocation ratio, not a cross-over design. The control group receives placebo for the first 3 days followed by functional fatty acids for the subsequent 3 days. The primary comparisons are: (1) between the experimental group (3 days of functional fatty acids) and the control group (3 days of placebo) at day 3; and (2) between the experimental group (6 days of functional fatty acids) and the control group (3 days of placebo + 3 days of functional fatty acids) at day 6.

This delayed-intervention design was chosen over a 6-day placebo-controlled design primarily for ethical reasons. Our pilot study demonstrated a 25% complete expulsion rate at day 3 with functional fatty acid treatment, and withholding a potentially effective intervention for the full 6 days would be ethically questionable. Additionally, this design allows us to evaluate both the short-term efficacy of the intervention (day 3 comparison: active treatment vs. placebo) and the effect of treatment duration (day 6 comparison: 6 days of continuous treatment vs. 3 days of delayed treatment). Importantly, the day 6 comparison is not between active treatment and placebo, but between two different durations of active treatment.

The core objective of this superiority design is to demonstrate that oral functional fatty acids (experimental intervention) are significantly more effective than the control intervention in promoting the expulsion of small gallbladder stones. This design was selected on the basis of the research hypothesis of the trial: preliminary evidence from preclinical studies and pilot data suggests that compared with the control intervention, functional fatty acids improve gallbladder motility and better regulate bile composition, thereby facilitating the passage of small stones.

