### Secondary objectives

In this study, relevant indices, including the volume of the gallbladder and the thickness of the gallbladder wall, will be compared among patients via ultrasound examinations before and after the intervention. The purpose of this study is to determine whether the intervention affects gallbladder contraction function and can alleviate gallbladder inflammation.

Moreover, we will compare the rates of clinical adverse events, such as abdominal pain and diarrhea, before and after the intervention. This comprehensive comparison will help us gain a more in-depth understanding of the impacts and safety implications of the dietary therapy studied in this trial.

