### Intervention description

Data pertaining to the small gallstones will be extracted from the electronic medical records of outpatients who underwent gallbladder ultrasound examination at this hospital. Follow-ups will be conducted via telephone. If a patient meets the inclusion and exclusion criteria, expresses willingness to participate, and has no clinical symptoms related to gallstones, a gallbladder ultrasound will be repeated by a trained and experienced sonographer. Only patients with gallstones measuring less than 2 mm at this follow-up examination will be eligible for enrollment. Eligible patients will be randomly assigned to the experimental group or the control group. The attending physician will explain the potential risks and benefits of the intervention, and written informed consent will be obtained from all participants.

The patients in the experimental group will take 50 mL of oral functional fatty acids on an empty stomach every morning for 6 consecutive days. In the control group, patients will first receive oral placebos for 3 days, followed by the same dose of oral functional fatty acids as the experimental group for the next 3 days. The blinded ultrasound physicians will perform gallbladder ultrasounds on the 3rd and 6th days after treatment to evaluate the effect of small gallstone expulsion. We chose the 3rd and 6th days after the intervention as the observation time points for evaluating the effect of small gallstone expulsion for the following reasons. On the basis of our experience and data from pilot studies, after 6 days of oral functional fatty acids, small gallstones were effectively expelled or exhibited a reduction in their content. However, it remains unclear whether the small gallstones were expelled precisely on the 6th day of intervention or before. Therefore, using the median value as a reference, we aimed to identify an optimal time point for evaluating the expulsion of small gallstones. Well-trained volunteers will follow up with patients during treatment to increase patient compliance and facilitate timely recording and management of any complications.

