#### Secondary outcome measures

Table 1 presents detailed information on the secondary outcome measurements. These data demonstrate the effectiveness and safety of the intervention process, as well as the potential risks.

**Table 1 tab2:** Secondary outcome measures.

Secondary outcome measure	Assessment time point	Operational definition
Gallbladder volume	7 days post-intervention	Measured by abdominal ultrasound using the ellipsoid formula: Volume = Length × Width × Depth × 0.52
Gallbladder wall thickness	7 days post-intervention	Measured by abdominal ultrasound at the thickest point, accurate to 0.1 mm
Serum total bilirubin	7 days post-intervention	Determined by standard laboratory assay; normal reference range: 3.4–17.1 μmol/L
Post-intervention abdominal pain	7 days post-intervention	Assessed using the Numerical Rating Scale (NRS)^1^; scores range from 0 (no pain) to 10 (worst imaginable pain)
Post-intervention acute pancreatitis	14 days post-intervention	Defined as the presence of characteristic abdominal pain plus serum amylase level ≥3 times the upper limit of normal^2^
Post-intervention gastrointestinal bleeding	14 days post-intervention	Defined as melena (black tarry stools) or a decrease in hemoglobin (Hb) level ≥20 g/L from baseline^3^
Post-intervention nausea, vomiting, and diarrhea	14 days post-intervention	Recorded as the daily frequency of each symptom during the 14-day follow-up period

^1^NRS: Numerical rating scale. A validated self-report pain assessment tool.

^2^Upper limit of normal for serum amylase at our institution: 100 U/L.

^3^Normal reference range for hemoglobin at our institution: 120–160 g/L (female), 130–175 g/L (male).

^4^All ultrasound examinations will be performed by two independent blinded sonographers with ≥10 years of experience in abdominal imaging. All laboratory tests will be conducted using standard methods at the Clinical Laboratory of the First Hospital of Lanzhou University.

Participant timeline please see Figure 2.

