### Statistical analysis

A predefined statistical analysis plan will be followed. All the statistical analyses will be conducted using IBM SPSS (Statistics 30.0.0). A *p* value of less than 0.05 will indicate statistical significance. Categorical variables will be reported as counts and percentages. Continuous variable data will be presented as mean ± standard deviation for normally distributed data, or median (interquartile range, IQR) for non-normally distributed data.

Analyses will be performed on both the intention-to-treat (ITT) population and the per-protocol (PP) population. The ITT population includes all randomized participants who received at least one dose of the intervention. The PP population includes only participants who completed the study protocol without major protocol violations.

The primary analysis will compare the complete expulsion rate of small gallbladder stones at day 3 post-intervention between the two groups using the chi-square test.

Key secondary analyses will include:

Comparison of complete expulsion rates at day 6 post-intervention between the two groupsWithin-group comparisons of changes in gallbladder volume and gallbladder wall thickness from baseline to day 3 and day 6Comparison of the incidence of adverse events between the two groups

For dichotomous variables, the chi-square test or Fisher’s exact test will be used as appropriate. For continuous variables, the independent samples t-test will be used for normally distributed data, and the Mann–Whitney U test will be used for non-normally distributed data.

After the last patient has completed the 30-day follow-up, a blinded endpoint adjudication committee will independently review all primary and secondary endpoint data.

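### Read with Table 1, the between-group adverse-event comparison sets 6 against 3 days of the same product, not active against placebo, and leans towards no difference

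*Protocol article*

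**What the plan says.** **Exposure.** The experimental arm takes "50 mL of oral functional fatty acids on an empty stomach every morning for 6 consecutive days" (Intervention description). For the other arm, "The control group receives placebo for the first 3 days followed by functional fatty acids for the subsequent 3 days" (Trial design). The arms table says the same. Days 1-3 are therefore the only period in which one randomized arm is on placebo.

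**Safety outcomes.** Table 1 (Secondary outcome measures) places the abdominal pain score and bilirubin at "7 days post-intervention". It places pancreatitis, gastrointestinal bleeding, nausea, vomiting and diarrhea at 14 days. The last three are "Recorded as the daily frequency of each symptom during the 14-day follow-up period".

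**Safety analysis.** The article describes it in three ways:
- Statistical analysis: a comparison "of the incidence of adverse events between the two groups", with no window given.
- Secondary objectives: "we will compare the rates of clinical adverse events, such as abdominal pain and diarrhea, before and after the intervention".
- Aims and objectives: incidence and severity of "treatment-related adverse events (such as gastrointestinal symptoms and abdominal pain) in the treatment group".

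**Acknowledged limit.** Trial design says that "the day 6 comparison is not between active treatment and placebo, but between two different durations of active treatment". No corresponding statement is made for safety.

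**The concern.** Safety is a stated aim alongside efficacy, and the placebo arm is what separates product effects from background symptoms. If adverse events are counted to the time points in Table 1, controls have by then been scheduled for three active doses. An effect that appears with the first few doses then arises in both arms, three days apart, and largely cancels. For a safety outcome, bias towards no difference is the unfavourable direction: a small difference could be read as reassurance against placebo when the comparison was not against placebo. The other two descriptions do not repair this, because neither a before/after comparison nor a summary of the treated group uses the placebo arm.

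**Working it through.** The article gives no figure for the adverse-event comparison, so there is none to reproduce. The check has two parts.

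**1. Which exposure falls inside each window**

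| Window | Experimental arm | Control arm |
|---|---|---|
| Days 1-3 | 3 active days | 3 placebo days |
| To 7 or 14 days (Table 1) | 6 active days | 3 placebo + 3 active days |

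It makes no difference whether the 7 and 14 days run from the first or the last dose: both fall after day 6.

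**2. Expected size of the contrast**

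Inputs:
- Diarrhea in the pilot: 2/20 = 10% over 6 active days (Background and rationale).
- 50 participants per group.
- Assumed: no background events. The pilot gives no onset days, so two onset patterns are shown.

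*All risk in the first three active doses.* Both arms receive three active doses, so the full window gives 10% versus 10%, a difference of 0. The difference is 0 whatever the true rate. Days 1-3 give 10% versus 0%, or about 50 × 0.10 = 5 events versus none.

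*Constant daily hazard.* Risk over d active days is 1 − (1 − 0.10)^(d/6). For d = 3 this is 1 − 0.90^0.5 = 5.1%.
- Full window: 10.0% versus 5.1%, difference 4.9 points.
- Days 1-3: 5.1% versus 0%, difference 5.1 points, or about 50 × 0.051 = 2.6 events versus none.

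*Reference.* A 6-day placebo arm would give 10% versus 0%, or 10 points, under either pattern.

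With an assumed 5% background risk over 6 days and a constant hazard, the full window gives 14.5% versus 9.9% (4.6 points), days 1-3 give 7.5% versus 2.5% (5.0 points), and a 6-day placebo would give 14.5% versus 5.0% (9.5 points).

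**Power of Fisher's exact test, 50 per group, two-sided 0.05, no background events.** Only the 10% rate comes from the article; 20% is an assumption.

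| 6-day risk on active | Pattern | Full window | Days 1-3 |
|---|---|---|---|
| 10% | first doses | 2% | 38% |
| 10% | constant hazard | 6% | 4% |
| 20% | first doses | 3% | 95% |
| 20% | constant hazard | 17% | 44% |

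In the first-dose rows the two arms have equal true full-window rates, so those full-window figures are false-positive rates.

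**The case against.** **The window is not in the analysis section.** The Statistical analysis section states none, and it refers to an analysis plan fixed in advance that is not shown. Period splits and treatment-emergent definitions are often left there. This stands in part: a reader might infer that the article prescribes a 14-day between-group test, and it does not. The point rests on reading two sections together. It is still more than absent detail, because the only safety time points the article gives lie after the control arm has switched.

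**The design hides harm.** A reader might infer this too, but the documents do not support it in that form. Complete masking needs all risk to fall in the first three doses, which the pilot does not show. Under a constant hazard, the full-window and days 1-3 differences are almost equal (4.9 and 5.1 points), and at 10% the test has almost no power in either window. Harm that depends on duration would still show in part. Data collection and management also has complications recorded daily, from the day before treatment to one month after, so the information is not lost.

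**Nothing uses days 1-3.** An unrestricted comparison includes those days. What is missing is a comparison that isolates them.

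**Later harms matter.** Data monitoring singles out stone impaction with obstructive jaundice or biliary pancreatitis. These may appear after day 3, and the 6-day versus delayed 3-day contrast is still randomized. This stands in full: a days 1-3 comparison should be added, not substituted.

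**The three descriptions can coexist.** A summary of the treated group and a before/after description do not bar a between-group comparison. This also stands. They need labels, not deletion.

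**Conclusion.** The concern holds as a bias towards no difference in the safety comparison. Taken together, Statistical analysis, Table 1 and the control regimen yield 6 versus 3 active days, and the article states that limit for day-6 efficacy only. At the pilot rate of 10%, without background events, the expected full-window difference lies between 0 (first-dose onset) and 4.9 points (constant hazard), where a 6-day placebo would give 10. That range rests on two assumed onset patterns and a rate from 2 of 20 patients.

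The documents do not show that harm would go undetected or be reported as absent. The primary day-3 efficacy endpoint is unaffected. The gain from a days 1-3 comparison is mainly that it is a true active-versus-placebo contrast. At a 10% rate it does not bring adequate power.

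**What to change.** 1. In Statistical analysis, add as the placebo-controlled safety comparison the events with onset from the first dose until just before the first day-4 dose. Report counts by arm and the risk difference with its confidence interval; with so few events expected, a p value alone would say little.
2. Keep the comparison over full follow-up, by arm, so that later-onset harms are captured. Label it 6-day versus delayed 3-day exposure, and state that it is not placebo-controlled, as Trial design already does for day-6 efficacy.
3. Label the treatment-group summary in Aims and objectives and the before/after comparison in Secondary objectives as descriptive, so that all three sections agree.
4. Confirm that the daily complication records in Data collection and management carry onset dates, and reconcile them with the Harms section, which lists visits at baseline and weeks 4, 8 and 12.

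**Cost.** For nausea, vomiting, diarrhea and recorded complications this is a change of wording, since daily recording is already planned. The days 1-3 window is short, with few events and low power at 10%. It does not cover the pain score or bilirubin, which Table 1 schedules only at 7 days; for those two the report should say that no placebo-controlled comparison is available.

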### Data monitoring

Given the excellent safety profile and short duration of this trial, a formal data monitoring committee (DMC) is not required. However, a dedicated safety monitoring team will conduct weekly reviews of all adverse event data throughout the study period.

Although the risk is low, we acknowledge the possibility that small gallstones may become impacted at the sphincter of Oddi, leading to obstructive jaundice or acute biliary pancreatitis. In such cases, the intervention will be immediately discontinued, and the patient will receive appropriate medical treatment according to standard clinical guidelines.

All serious adverse events will be reported to the Institutional Ethics Review Board within 24 h of occurrence. *Ad hoc* safety analyses will be performed if any unexpected safety signals emerge.

### Auditing

An auditing committee consisting of a surgeon and a sonographer will monitor the trial at least quarterly. The committee, independent of the investigators, is responsible for auditing the trial’s frequency, procedures, and safety. All adverse events thought to be related to the trial will be recorded rigorously and carefully. Any unexpected major serious complications suspected to be associated with the intervention will be reported to the interviewer and attending physicians, the trial may be temporarily stopped, and effective treatment measures will be taken by the attending physicians.

### Quality assurance

To enhance the standardization and consistency of this single-center RCT, a comprehensive Standard Operating Procedure (SOP) has been developed that governs all processes from registration, randomization, intervention administration, data collection, and sample management. All the participating personnel, including physicians, nurses, assessors, and trial coordinators, will undergo rigorous SOP training and be required to strictly adhere to the protocol’s guidelines.

### Ethics and dissemination

Each participant provided written informed consent before data collection. The study was approved by the Ethics Committee of the First Hospital of Lanzhou University (LDYYLL-2024-804). Any changes to the eligibility criteria, outcomes, and analyses must obtain approval from the ethics committee. All procedures in the trial will be performed in accordance with the ethical standards of the institutional and/or national research committee and with the 1964 Helsinki declaration and its later amendments or comparable ethical standards.

### Patient and public involvement

Neither the patients nor the public were involved in the design, conduct, reporting, or dissemination plans of this research.

### Confidentiality

Data will be handled confidentially. During the whole experiment, sensitive information such as patient name and identity card number will not be revealed by coding.

### Availability of data and materials

Upon trial completion, the researcher will promptly write and submit the manuscript via open access. Each participant will be mailed the results and conclusions. Owing to patient confidentiality considerations, the raw data from this study are not publicly available. Researchers with a justified need for access may request the data from the corresponding author, subject to appropriate ethical and regulatory approvals.

### Dissemination policy

Data analysis, interpretation, and findings will be presented at academic conferences and published in peer-reviewed journals. As no data from the individuals has been reported within the manuscript, consent for publication of images may not be needed. Neither the patients nor the public were involved in the design, conduct, reporting, or dissemination plans of this research.

## Discussion

To our knowledge, this will be the first prospective, single-center, double-blind, randomized controlled trial to evaluate the therapeutic potential of functional fatty acids in the management of gallbladder calculi. Without timely intervention, small gallbladder stones may progress to form gallstones, leading to a range of health and economic burdens. These include pain-related reductions in quality of life, impaired gallbladder function and the inconvenience and risks associated with surgical removal (24).

To date, several small-scale studies have explored the use of diet or proprietary Chinese medicine for treating gallbladder stones (25). Although some patients in these studies were able to successfully excrete the gallstones, there is a notable lack of evidence-based medical evidence. Consequently, these treatment methods are neither widely promoted nor used in clinical practice. This can be partly due to the limitations of diet therapy, such as the inability to precisely identify gallbladder stone components, the absence of placebo control, and the difficulty of accurately quantifying the diet.

In the pilot study of this research, six patients with sonographically confirmed gallbladder small stones successfully excreted their stones following dietary therapy. The intervention was well tolerated, with only two patients experiencing mild diarrhea after consuming functional fatty acids and no other complications reported. On the basis of these findings, we believe that dietary therapy may hold promise as a treatment option for patients with small gallstones.

A possible biological mechanism underlying the efficacy of functional fatty acids in promoting gallstone expulsion involves multiple complementary pathways:

*Stimulation of cholecystokinin (CCK) secretion*: Medium-chain triglycerides (MCTs) are rapidly absorbed in the proximal small intestine, stimulating intestinal I cells to secrete CCK—the primary hormone regulating gallbladder motility. CCK induces strong, coordinated contraction of the gallbladder smooth muscle while simultaneously relaxing the sphincter of Oddi, creating a pressure gradient that facilitates the passage of small stones into the duodenum. Long-chain triglycerides (LCTs) provide a more sustained stimulation of CCK secretion, maintaining gallbladder contractility over an extended period.*Enhanced gastrointestinal motility*: Functional fatty acids promote intestinal peristalsis, which indirectly increases biliary tract motility and accelerates the transit of stones through the common bile duct.*Modulation of bile composition*: Functional fatty acids may alter the lipid profile of bile, reducing cholesterol saturation and inhibiting the further growth of cholesterol stones. In some cases, they may even partially dissolve small cholesterol microliths, making them easier to expel.*Anatomical safety*: The selection of stones <2 mm in diameter ensures anatomical feasibility for passage through the cystic duct (2–3 mm) and common bile duct (6–8 mm), minimizing the risk of biliary obstruction, acute cholangitis, or pancreatitis.

Ultrasound has a high sensitivity for detecting gallstones, but it cannot distinguish between cholesterol and pigment stones solely on the basis of imaging features (26). Therefore, we did not perform relevant analyses on the nature of the stones in this study.
